### Trial outcomes

Considering the objectives of the HERrespect intervention, four primary outcomes, split into two groups, were identified:Three primary outcomes are focused on: physical, sexual, and physical and/or sexual IPV experienced by female garment workers in the past 12 months:The proportion of women experiencing any physical IPV from husband during the past 12 months.The proportion of women experiencing any sexual IPV from husband during the past 12 months.The proportion of women experiencing severe physical and/or sexual IPV from husband during the past 12 months.

These outcomes are being measured using a set of questions based on the World Health Organization (WHO) violence against women instruments, which are designed to minimize reporting biases that arise from subjective perceptions of abuse by asking only about specific behaviours perpetrated by a male partner. The questions have been adapted for the “What Works To Prevent Violence against Women and Girls?” Global Programme and are being used across the evaluations within the programme.2.Violence witnessed or experienced at workplace in the past 4 weeks by female garment workers: This outcome is being assessed with an 8-item scale asked to the female garment workers, which was loosely developed as an adaptation of the peer victimisation scale [24]. The adaptation has been to measure ‘experiencing or witnessing’ victimisation as this was deemed to be less sensitive with factory management than actual reported victimisation. The adaptation of questions drew heavily on the findings of the formative research on the types of violence which occur in the work place.

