Severe physical and/or sexual IPV during past 12 months	Questions asked for measuring physical and sexual violence during past 12 months	Never, once, few, many	10	–	–	Binary - never compared to once or more	Decrease
Witnessed or experienced workplace violence	In the past four weeks, how often have you experienced or witnessed a manager call a worker names?	Never, once, 2-3 times, many times	8	0.83		Mean	Decrease
Secondary outcomes							
Gender attitudes and responses to violence							
Acceptance of VAWG among female workers	In your opinion, does a man have good reason to hit his wife if she disobeys him?	4-point Likert: Strongly disagree, disagree, agree, strongly agree	6	0.69	–	Mean	Decrease
Positive gender attitudes among management staff	I think that a woman needs her husband’s permission to do paid work.	4-point Likert: Strongly disagree, disagree, agree, strongly agree	13	–	0.68	Mean	Decrease
Response to IPV	Did you go to any person/place for help when you experienced any physical or sexual violence during last 12 months?	Yes, no	1	–	–	Binary – yes compared to no	Increase
Knowledge of services in response to IPV	Do you know from where one can get help for such experience? If yes, where?	Yes, no	1	–	–	Binary – yes compared to no	Increase
Women’s well-being							
Self-esteem of the female garment workers	At times, You think you are no good at all.	4-point Likert: Strongly disagree, disagree, agree, strongly agree	10	0.76	–	Mean	Increase
Depression among female garment workers during past week	During the past week you thought your life had been a failure.	Rarely or none of the time; some or a little of the time; moderate amount of time; most or all of the time	13	0.87	–	Mean	Decrease
Management knowledge, practices and experiences							
Better management style of management staff	If you do not comply with your supervisor, you will not be rewarded	Very unlikely; Somewhat likely; Very likely	14	0.90	–	Mean	Increase
Correct knowledge regarding laws and policies	Are there laws/policies in this country that protect women from spousal violence?	Yes; no; don’t know	5	–	–	% correct compared to % incorrect	Increase
Positive attitudes regarding laws and policies	To your opinion - “Sexual remark and gesture is an act of workplace violence”	Strongly agree; agree; no opinion; disagree; strongly disagree	5	–		Mean	Increase

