### Sample size

For the worker survey, the sample size calculation was based on the primary outcome – physical IPV against female garment workers. Expecting 56% baseline prevalence of past year physical IPV experienced by the female garment workers (icddr,b unpublished data), and anticipating a 20% effect size, 5% level of significance and 80% power, the required sample size was 330 workers for both the intervention and control groups. To account for a 20% lost to follow up the sample size increased to 396 workers for both the groups, which was rounded up to 400. Thus, a sample of 100 workers would be required from each of the intervention and control factories, giving 800 in total.

For the management survey, the sample size calculation was based on gender inequitable attitudes among garment management staff. Anticipating 50% baseline prevalence of high or moderate gender equitable attitudes among the management staff, a 30% effect size, 5% level of significance and 80% power, the required sample size was 183 management staff for both intervention and control groups. Anticipating 10% loss to follow up, the sample size increased to 200 for both the groups. Thus a sample of 50 management staff would be required from each of the intervention and control factories, giving 400 in total.

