### Statistical methods: Data analysis

Intention-to-treat (ITT) analysis will be used for assessing the impact of HERrespect. Thus, all the workers selected for the study will be included in the analysis. The primary analysis will involve comparison between intervention and control factories for assessing the impact of full HERrespect intervention (group sessions and factory-wide mobilization) over control. First the data from intervention and control factories and baseline and endline samples will be compared and Chi-square (for categorical variables) and t-tests (for continuous variables) will be performed to test whether there are differences in prevalence of background characteristics. If differences between intervention and control factories and baseline and endline samples are evident, the pre-existing differences will be controlled in subsequent analyses. The impact of HERrespect intervention on main outcomes of interest will be assessed using risk ratios derived from binary regression analyses adjusting for baseline rates. All analyses will be adjusted for the potential factors associated with the outcomes of interest. The same approach will be followed for assessing the secondary outcomes.

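### The stated effect model, risk ratios from binary regression, cannot be applied to the eight of fourteen outcomes that Table 2 scores as means, including the workplace-violence primary outcome

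*Protocol article*

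**What the plan says.** The section on statistical methods gives one model for intervention effects: "The impact of HERrespect intervention on main outcomes of interest will be assessed using risk ratios derived from binary regression analyses", adjusted for the baseline rate. It then says that all analyses will also be adjusted for factors associated with the outcomes, and closes with "The same approach will be followed for assessing the secondary outcomes". No exception is made for scale scores. The only method for continuous data in that section concerns the comparability of the samples: "t-tests (for continuous variables) will be performed to test whether there are differences in prevalence of background characteristics".

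The section on trial outcomes says that "four primary outcomes, split into two groups, were identified". Three are past-year partner-violence outcomes, which Table 2 scales as binary. The fourth is violence witnessed or experienced at work: "This outcome is being assessed with an 8-item scale asked to the female garment workers". Its sample item in Table 2 reads "In the past four weeks, how often have you experienced or witnessed a manager call a worker names", with four ordered frequency responses, and the scaling column gives a mean. Seven of the ten secondary outcomes have the same entry in that column.

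The sample-size section plans the management survey on a proportion: "Anticipating 50% baseline prevalence of high or moderate gender equitable attitudes among the management staff". Table 2 scores the management gender-attitude outcome as the mean of 13 items.

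**The concern.** Two statements in the article do not fit together. One fixes how each outcome is scored, and the other fixes how effects are estimated. For the mean-scored outcomes the second cannot be carried out on the first. This is more than a missing detail, because the article names a model and expressly carries it over to outcomes that it defines as means.

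The most important of these is workplace violence. It is one of the two primary objectives, and the only primary outcome for the workplace half of the trial. As written, it has no analysis that can be run on its defined score. If the conflict is settled only once endline data are available, the choice of model, and of any cut-point, could be influenced by the results. The article states that nobody was blinded to arm, so it is worth closing that choice in advance.

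**Working it through.** **Step 1. Set the scaling in Table 2 against the stated model.**

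| Outcome | Scaling in Table 2 | Is a risk ratio defined? |
|---|---|---|
| Physical partner violence (primary) | Binary | Yes |
| Sexual partner violence (primary) | Binary | Yes |
| Severe physical and/or sexual partner violence (primary) | Binary | Yes |
| Workplace violence (primary, 8 items) | Mean | No |
| Acceptance of violence, workers (6 items) | Mean | No |
| Gender attitudes, management (13 items) | Mean | No |
| Response to partner violence | Binary | Yes |
| Knowledge of services | Binary | Yes |
| Self-esteem (10 items) | Mean | No |
| Depression (13 items) | Mean | No |
| Management style (14 items) | Mean | No |
| Knowledge of laws and policies (5 items) | Percent correct | Unclear |
| Attitudes to laws and policies (5 items) | Mean | No |
| Burnout (16 items) | Mean | No |

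Count of mean-scored outcomes: 1 of 4 primary + 7 of 10 secondary = 8 of 14. Knowledge of laws is not counted. If it is a percent-correct score per person, it would be a ninth.

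**Step 2. Why the model does not fit.** The stated estimate is a ratio of two risks, "will be assessed using risk ratios derived from binary regression analyses adjusting for baseline rates". A risk is the probability of a yes/no event. Table 2 gives no codes for the workplace-violence responses, so assume 0 to 3. The eight items then sum to 0 to 24, and the mean has 25 possible values between 0 and 3. Only two of them, 0 and 1, are legal values for a yes/no variable. With codes 1 to 4 there are again 25 values, from 1 to 4, and only one is legal.

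**Step 3. Illustration with simulated data.** This used 400 respondents per arm, eight items coded 0 to 3 and each code equally likely. These are assumptions, not trial data.
- Scores ran from 0.375 to 2.75, and 5.75% of them equalled 0 or 1.
- A logistic fit was refused because values lay outside the unit interval.
- A binomial fit with log link returned an intercept of 0.421 and an arm coefficient of -0.033. The fitted control-arm value is exp(0.421) = 1.52, which cannot be a risk. The exponentiated arm coefficient, exp(-0.033) = 0.97, is at best a ratio of means.

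**Step 4. The management sample size.** Inputs from the sample-size section are 50% at baseline, a 30% effect (read as relative, so 50% against 35%), 5% significance and 80% power.
- Uncorrected: n = [1.960 × √(2 × 0.425 × 0.575) + 0.842 × √(0.50 × 0.50 + 0.35 × 0.65)]² / 0.15² = 169.3, so 170 per arm.
- With continuity correction: n = (169.3 / 4) × [1 + √(1 + 4 / (169.3 × 0.15))]² = 182.4, so 183 per arm, which is the article's figure.

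The management survey was therefore sized by comparing two proportions. The article gives no cut-point that defines the proportion.

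**The case against.** The article is a condensed account, and an analysis plan that is not shown may name a model for each scale. The phrase about main outcomes is not defined and could mean the partner-violence outcomes, on one of which the worker survey was sized. The words about the same approach could refer only to the general scheme: intention to treat, comparison of arms, and adjustment for baseline and covariates.

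Some of this stands. The wording is loose, and an analyst would probably not run a binary model on a mean score. But the narrow reading leaves workplace violence with no stated effect analysis, while the seven mean-scored secondary outcomes still come under the carried-over approach. A later plan would have to overrule the article's sentence, not merely fill it in.

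A reader might go further and infer three things that the documents do not support.
- That the plan commits to dichotomising the scores, with cut-points picked after the fact. It does not say so. Table 2 marks these outcomes as means and others as binary, so dichotomising would itself break a stated rule.
- That about 36% of the information would be lost. That figure (1 - 2/π) assumes a roughly normal score split at its median. The article gives no distribution and proposes no split, and a four-week frequency scale may well be skewed.
- That the management sample size contradicts Table 2. Sizing on a prevalence and analysing a mean are compatible if the prevalence is only a planning device. The article should say so.

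Whether inference should allow for factory clustering is a separate question that this mismatch does not settle. Linear regression is also not the only possible repair. Cut-points defined in advance, with Table 2 amended to match, would remove the conflict, but at the price of discarding information.

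**Conclusion.** The point holds as an inconsistency within the article. The only effect model it names cannot be applied to 8 of 14 outcomes as Table 2 defines them: one of four primary and seven of ten secondary. The count rests on the scaling column of Table 2 and on reading the main outcomes to include all four primary outcomes. On the narrower reading, workplace violence has no stated effect model, so all eight still lack a usable one.

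No numerical loss of power or precision can be attached to this, because score distributions and cut-points are not given. The analyses of the three partner-violence primary outcomes are untouched, and no sample size changes.

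**What to change.** Replace the sentence that carries the approach over to the secondary outcomes with two rules.
- **Binary outcomes:** risk ratios, as now stated.
- **Every outcome that Table 2 scores as a mean, workplace violence first:** linear regression of the endline score on arm, adjusted for the respondent's own baseline score and the planned covariates, reporting the adjusted mean difference with its 95% confidence interval. Where a score is markedly skewed, robust standard errors may be needed.

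State which rule applies to knowledge of laws and policies. Add to the sample-size section that the prevalence used for the management survey was a planning proxy for the mean attitude score.

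The cost is a few sentences and no new data. The article places the endline survey in September to November 2018. The rules should be fixed, at the latest, before endline data are analysed.

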### Ethics and dissemination

The study received approval from the Institutional Review Board (IRB) of icddr,b and the South African Medical Research Council Ethics Committee. The participation of the intervention and control factories was based on the factories’ consent to be a part of the study. This study is fully guided by the WHO recommendations for ethical considerations in researching violence against women [35].

Attention was paid when designing the questionnaire to carefully and sensitively introduce and enquire about workers’ experiences of violence and to ensure that questions are framed in a manner that is non-judgmental. There is evidence in the literature that many factory management is opposed to the disclosure of workplace violence and workers disclosing or attempting to address it are victimized through threats, harassment and dismissal [18]. Therefore questions on workplace violence were included in a style which was as far as possible non-threatening to the factory management.

Individual verbal consent was sought by the interviewer prior to the interview with each female garment worker and management staff (see Additional files 3 and 4). All participants were informed orally of the purpose and nature of the study, its expected benefits, sensitivity, confidentiality and voluntary nature of participation. They were asked to give oral consent to participate. Participation in the study was entirely voluntary. The respondents were also free to terminate the interview at any point, and to skip any questions to which s/he did not wish to respond. Written consent was not used due to low levels of readability and concerns regarding confidentiality.

Each interviewed female worker received $6.5 (BDT 500) for participating at the baseline survey. Again at endline $8.5 (BDT 650) will be offered in compensation for their time. The physical safety of interviewees and interviewers from potential retaliatory violence by the perpetrator was of prime importance. If the focus of the research becomes widely known - either within the factory or household or among the wider community it may risk the safety and security of both. Thus, at the factory level the intervention and the study were introduced as focusing on addressing IPV and improving management and in the family and community it was framed as a survey of factory work management and female workers life experiences.

All the study participants were given a unique code and all the indentifying information are kept in a separate file exclusively accessed by the research team and used for tracking the individuals over the intervention period and to contact them during the endline survey. Care will be taken to present the research findings in sufficiently aggregated form to ensure that no participating factories and workers can be identified.

### Limitations

There are constraints on research in the ready-made garment industry in Bangladesh which had to be accommodated in the study design. Factories had strict preference for being included in the study as an intervention or control factory, which the study had to adhere to. This precluded use of a randomisation into the study arms. This means that confounders could not be allocated between arms using randomisation and so have to be measured and adjusted for in analysis where possible. We cannot be sure that all confounders will be measured and adjusted for, but focus on the main possible ones. This will slightly weaken our confidence in the results but having some comparison arm is a strength even if allocation to arm was not random.

We had to take into account the real circumstances of location on the ground and were also not able to match intervention and control factories by location. We have no reason to believe this will affect the results.

In one factory, the number of eligible workers was less than 100. Therefore we recruited all possible eligible workers (77) and relaxed the criteria of duration of employment from 12 to 10 months (23). This is unlikely to impact the results.

The sample (50) for the management survey was selected by participating factories except in one, where the number of management staff was lower than the requirement, so all management were recruited. We recognize that biases may have been introduced in the management sample due to purposive selection conducted by the factories. Any factory approached with such an intervention is likely to use the same strategy of worker and management staff selection. As the intention is to assess impact of an intervention that is feasible to implement and can be scaled up in future, the current sample selection strategy would show the real impact of such intervention.

It is possible that we will find it hard to deliver the full dose of the intervention in factories if managers are reluctant to release workers and managers for periods of 2-3 h for sessions and some simple amendments to sessions may be needed to accommodate available time. This may impact intervention fidelity and ultimately impact.

The primary and secondary outcomes are based on self-reporting and we cannot know if there is under-reporting. This is always a risk in questionnaire-based outcomes and especially where participants may feel the need to protect their family by under-reporting partner violence or may fear reprisals for accurate reporting of workplace violence. We have taken very considerable care around confidentiality, including interviewing women outside work, and hope this will minimise these under-reporting risks.

We have accommodated some loss to follow up in the sample size calculation, but job mobility is a feature of the industry and we are concerned that more women and managers may leave the factories than anticipated. Also any staff leaving intervention factories during the intervention would not get the full dose. Intention to treat requires cohort follow up but mobility may dilute apparent impact. Further absolute loss to follow up will reduce the study’s power to detect the anticipated difference between arms.

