### Trial design

The trial employs a quasi-experimental design. It is being conducted in four intervention and four control factories. In the intervention factories a randomly selected cohort of married female line workers, a cohort of male line workers, and all middle management staff received the main intervention. In addition, factory-wide campaigns were carried out, and a community activity in one intervention community. For the evaluation, two cohorts have been established and will be followed up over 24 months in each of the intervention and control factories. One is a cohort of randomly selected female line workers (100 per factory) and the second is a cohort of selected management staff with frequent interaction with workers (50 in each factory). Two different questionnaires are administered for workers and management staff (see Additional files 1 and 2). All the workers and management staff from these cohorts were interviewed at baseline, and will be interviewed in the endline. The baseline was conducted before the intervention started, while the endline will be conducted 24 months post-baseline.

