### Eligibility criteria

Workers were eligible for the research if they were currently married and living with husband (necessary for measuring IPV) and had been working in the current factory for at least one year. All management staff in the factory management were eligible to participate in the study.

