### Recruitment and allocation

BSR works with a network of international brands and buyers via HERproject, a women empowerment initiative in the supply chain, in Bangladesh, and both intervention and control factories in HERrespect were recruited through buyers as per the selection criteria, through one-on-one engagement and a suppliers’ workshop. Four buyers participated in nominating eight factories (four intervention and four control) to join HERrespect. Participant factories had strict preference for being included as an intervention factory or control factory and were recruited on that basis. Care was taken to select control factories at a distance from the intervention factories to prevent potential contamination. Also, preference was given to factories that had not recently completed similar training programs or interventions in gender-based violence.

Each factory provided a self-selected list of 315 workers from their full list of workers. A listing was then carried out of these selected 315 workers within each factory mainly for the purpose of screening eligibility. Once eligibility had been established and agreement to participate given, 100 workers were randomly selected from each factory. The workers from the intervention factories were then assigned to group sessions and interviewed at baseline. If more than one worker belonged to the same household, one was chosen randomly for participating in the study. Each factory provided a self-selected list of 50 management staff having direct interaction with workers. This cohort of management staff are interviewed at baseline and endline. However, all management staff received the group sessions.

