#### Data collection methods

Baseline data were collected between September to December 2016 using face-to-face interviews, with Personalized Digital Assistants (PDAs) to reduce data entry error as logic checks were built in. Workers’ interviews were conducted in private in a location convenient for participants outside the factory. According to the study participants’ choice 98% of workers were interviewed at their own home and 2% of them were interviewed outside of their home (e.g., relatives or neighbours home, Non-Government Organisation (NGO) office, etc.). The interviews took place in the evening after work during work days and in the day time during weekends and holidays. The usual time of the interviews was between 7 and 10 pm on work days and 9 am to 4 pm on weekends and holidays. The interviewers phoned the participants a day before the target interview date to schedule the interview and obtain directions for the interview venue. The interviews with the management staff were conducted in private within the factory during office hours. The appointments were arranged in advance.

Workers and management staff who were not available to be interviewed during baseline data collection were replaced. The replacement of a worker was done by randomly selecting another eligible worker from the same factory and the replacement of a management staff was done by the factory itself. But no replacement was made after the data collection had been completed.

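### The claim that factory-picked managers show the intervention's real impact does not follow, because the picking decided who was interviewed and not who was trained

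*Protocol article*

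**What the plan says.** - Limitations: letting factories pick their managers may have biased the management sample. Any factory offered the programme would probably pick workers and managers in the same way, and therefore "the current sample selection strategy would show the real impact of such intervention".
- Recruitment and allocation, on who was interviewed: "Each factory provided a self-selected list of 50 management staff having direct interaction with workers". This cohort is interviewed at baseline and endline.
- Same section, on who was trained: "However, all management staff received the group sessions". Trial design says the same in slightly narrower terms for the intervention factories: "all middle management staff received the main intervention".
- Data collection methods, on managers who were unavailable at baseline: "the replacement of a management staff was done by the factory itself".
- Limitations, on the one exception, a factory "where the number of management staff was lower than the requirement, so all management were recruited".
- Blinding and Recruitment and allocation: nobody was blinded, and factories joined the arm that they preferred.

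**The concern.** The scale-up defence works when selection is part of delivery. If factories will always choose who attends, then a trial in which they chose who attended estimates the effect that a roll-out would have. For managers, selection was not part of delivery. The sessions went to all of them, and the list decided only whose answers count.

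That is selection for measurement. It was done by factories that had chosen their arm and knew it. The section first discloses the bias and then cancels the disclosure with an argument that does not apply.

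At stake is the population to which the four manager-reported secondary outcomes refer. A reader who accepts the sentence would take results in nominees as the effect on all trained managers, and as the effect to expect at scale.

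**Working it through.** **The plan's own figures.** Table 3 has 195 intervention and 200 control managers; 195 + 200 = 395, as in Results. The plan was 50 per factory. The required 183 per arm also reproduces, reading the 30% effect as relative (50% to 65%), two-sided 5%, 80% power:

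- n = [1.960 × √(2 × 0.575 × 0.425) + 0.842 × √(0.25 + 0.2275)]² / 0.15² ≈ 169.3, which rounds up to 170;
- with continuity correction, (169.3 / 4) × [1 + √(1 + 4 / (169.3 × 0.15))]² ≈ 182.4, which rounds up to 183.

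The point does not rest on this figure.

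**Step 1. Treated against measured.**

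| Group | Who received the group sessions (intervention factories) | Who was interviewed | Did the factory's choice decide treatment? |
|---|---|---|---|
| Workers | Workers drawn at random from the eligible on a factory list of 315 | The same 100 per factory | In part: the list fed both |
| Managers | All management staff (or all middle management) | The factory's list of 50, with factory-chosen replacements | No |

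The scale-up argument has some force in the first row and none in the second.

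**Step 2. What the survey estimates.** Let f be the share of trained managers who were nominated for interview, D1 the effect in nominees and D0 the effect in the others.

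- Effect on all trained managers = f × D1 + (1 − f) × D0.
- Effect seen in nominees = D1.
- Difference = (1 − f) × (D1 − D0).

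The difference is zero if every manager was listed (f = 1) or if nominees and others respond alike. As f falls, it approaches the whole of D1 − D0. The article gives neither f nor the number of managers per factory, so no numerical value can be attached.

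**Step 3. How many were nominees.** All factories but one supplied a list.

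- Control: 200 = 4 × 50. A control factory with fewer than 50 managers would need another control factory above 50, which a list of 50 does not allow.
- Intervention: 195 = 3 × 50 + 45.

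The exception factory is therefore probably in the intervention arm, with 45 managers if the other three reached 50. It could have had up to 49 if those three were together up to four short. On these counts:

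- full-roster share of the intervention arm: 45/195 = 23% (49/195 = 25% at the upper end), against 0/200 in control;
- factory nominees overall: (395 − 45)/395 = 350/395 = 89% (346/395 = 88% at the other end).

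**The case against.** The strongest reply is that the article already admits the bias, that the sentence also covers workers, for whom it is more defensible, and that only secondary outcomes are touched. All three are true. They limit the weight of the point but do not rescue the inference for managers, since the admission is followed at once by a reason to disregard it.

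It is also fair to say that not every part of the programme reached every manager: joint sessions took 10 middle managers, and senior management had a two-hour awareness session. The article does not say that the interview list decided either.

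A reader might infer more than the text supports:

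- **A conflict in eligibility.** Eligibility criteria says "All management staff in the factory management were eligible to participate in the study", while Trial design describes "a cohort of selected management staff with frequent interaction with workers (50 in each factory". The first defines a pool and the second a subset listed from it. That is not a contradiction.
- **Managers without worker contact in the exception factory.** The article says only that all were recruited. It does not say that any lacked contact with workers.
- **An established difference between arms in the sampling rule.** The exception factory's arm is inferred from the counts and is not stated. If the other factories had few managers beyond 50, their lists would be close to full rosters anyway.
- **A shift in the treatment effect from mixing roster and nominees.** If nominees scored 0.3 SD better (an assumption), the level in the intervention arm would differ by 0.23 × 0.3 = 0.07 SD. This is a gap in level that would be present at baseline. Statistical methods adjusts for baseline and applies the same approach to secondary outcomes, so a stable gap would largely be absorbed. It would also run against the intervention. The figure should not be used as a bias estimate.

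Baseline adjustment does not deal with nominees who respond to training differently, and it does not make nominees represent the managers who were not interviewed.

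**Conclusion.** The real-impact inference is wrong as written for managers, and it is the article's own account of delivery that contradicts it. The conclusion rests on the statements that all (or all middle) management received the sessions and that the factory's list defined the interview cohort. It needs no numerical assumption.

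The scope is four manager-reported secondary outcomes. Management style is reported by workers and is unaffected, as are all primary outcomes. The direction and size of any bias are unknown. The counts of about 89% nominees overall and 23% full roster in the intervention arm assume 50 managers in every factory except one. This is a modest point about what may be concluded. It does not show that the manager results will be biased.

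**What to change.** 1. In Limitations, restrict the scale-up argument to workers and remove the real-impact inference for managers.
2. State there, and wherever the manager results are reported, that gender attitudes, knowledge of laws, attitudes to laws and burnout were measured mainly in managers nominated by their factories, and may not represent the effect on all trained managers.
3. Optional: repeat the manager analyses without the factory that recruited all its managers, after confirming its arm. An analysis plan that is not shown may already contain this, so its absence is no fault. Limiting that factory to managers with direct worker contact is not proposed, because the article does not show that such a variable was collected.

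The first two items cost a few sentences and a more modest claim. The third needs no extra data collection but loses precision: if the factory is in the intervention arm, three intervention factories would face four controls.
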